## Discussion

### Principal Findings

This study aims to evaluate the viability and efficacy of a predictive model designed to estimate the duration of a rehabilitation process and predict the likelihood of early, late, or no relapse in substance use, based on the digital phenotype of SUD. The hypothesis posits that an AUC of ≥0.80 and F2 of ≥0.8 will demonstrate that data collected from an affordable commercial smart band, demographic questionnaires, psychological tests included in the institution’s base protocol, and the proposed use of FER combined with valence and emotional activation scoring during craving episodes can effectively support the creation of this predictive model.

The potential of this project is supported by several premises. Wearable devices have become increasingly accessible and seamlessly integrated into daily life. As of January 2024, GSMA Intelligence reported 125.4 million cellular connections in Mexico, and GWI estimated that 31% of internet users aged 16-56 years use a smartwatch or smart band [81]. Considering that the device used in this study is among the most affordable commercial smart bands and compatible with any mobile operating system, the development of a viable predictive model could introduce this tool as a complementary aid in SUD rehabilitation, enhancing the effectiveness of treatment strategies.

Wearable devices and MLM have been successfully applied to various mental health conditions. For example, passive physiological activity measurements and MLMs have distinguished depressive patients from healthy controls by correlating variations in circadian rhythms, nocturnal HR, and higher depression test scores [30]. Similarly, MLMs using passive data have predicted depressive, manic, or hypomanic episodes in patients with bipolar disorder (BD) by identifying sleep disturbances, circadian rhythm changes, and physical activity variations [82]. Furthermore, facial emotion recognition combined with MLMs has been used to diagnose and predict alexithymia with an AUC of 0.80 [83]. In the context of SUD, MLMs have demonstrated potential by evaluating participant engagement, correlating stress and craving during recovery, and providing insights into treatment outcomes [84].

Psychological assessments remain a cornerstone for diagnosing and quantifying symptom severity in SUD, projecting recovery trajectories, and supporting research protocols. The psychological tests included in this study have been previously validated in SUD research, translated into Spanish, and recommended for clinical and diagnostic use [85-90]. Despite potential biases in self-reports, these tools have also been engaged in mental disorders such as schizophrenia and mood disorders like major depression and BD to develop MLMs and support symptom monitoring through digital technologies [30,46,60,91-96].

Digital tools for long-term symptom monitoring and clinical support during remission have been widely accepted in studies involving high-risk populations. For example, US veterans at risk of suicide provided valuable data on physiological activity and behavioral patterns surrounding suicide attempts through digital monitoring [64]. Similarly, high levels of acceptance have been observed among patients with BD, schizophrenia, anxiety, and major neurocognitive disorders, highlighting the feasibility of using such technologies in mental health research and clinical practice [34,37,56,60,93,97-102].

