### Algorithms

Modeling will be conducted using MATLAB, with ANN serving as the base algorithm. Additional algorithms, including decision trees, random forests, and support vector machines, will be used for validation. This multialgorithm approach will facilitate a comprehensive comparison of predictive accuracy across various models.

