### Validation and Verification

All models and algorithms will undergo validation, verification, and testing using MATLAB’s tools for model evaluation and hyperparameter optimization. These processes will assess precision, performance, and recall metrics. Optimal model performance will be defined by achieving an area under the curve (AUC) of ≥0.80 and F2 score of ≥0.8.

The output categories will serve as benchmarks to evaluate the validity, reliability, and precision of the models. The validation dataset will be used to perform initial comparisons both within individual models of each algorithm and across different algorithms, replicating models with distinct architectures to refine performance.

For model verification, the test dataset will be used to determine final AUC and F2 scores. This final evaluation will confirm the models’ effectiveness as ML tools for predicting rehabilitation outcomes and informing clinical decision-making.

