### Outcomes

#### Profiles

A total of 4 distinct subprofiles will be generated based on the results of the statistical analysis: (1) demographic, (2) psychological, (3) craving, and (4) digital biomarkers. These profiles will subsequently be integrated to create digital phenotypes for individuals with SUD.

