#### Predictive Model

A predictive model will be developed to distinguish between healthy individuals and patients with SUD. In addition, the model will predict the duration of a rehabilitation therapeutic program and the length of sobriety adherence for individuals rehabilitated using the center’s methodology. A minimum performance threshold of AUC≥0.8 and F2≥0.8 has been established to evaluate the model as fully functional.

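### The AUC/F2 threshold judges only the combined model, so meeting it cannot show that the smart band or facial emotion recognition contributes anything

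*Protocol article*

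**What the plan says.** The Discussion (Principal Findings) states the hypothesis and its criterion in one sentence: "The hypothesis posits that an AUC of ≥0.80 and F2 of ≥0.8 will demonstrate that data collected from an affordable commercial smart band". Alongside the band, that sentence names three further sources: the demographic forms, the centre's routine psychological battery, and FER paired with participants' ratings of the images. Of all of these taken together it says that they "can effectively support the creation of this predictive model". The next paragraph turns to the device: "the development of a viable predictive model could introduce this tool as a complementary aid in SUD rehabilitation".

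The same cut-off stands in two other places. Validation and Verification has "Optimal model performance will be defined by achieving an area under the curve (AUC) of ≥0.80 and F2 score of ≥0.8". Outcomes, Predictive Model has "A minimum performance threshold of AUC≥0.8 and F2≥0.8 has been established to evaluate the model as fully functional". Neither names a reference model.

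Under Outcomes, Profiles, four subprofiles are built (demographic, psychological, craving, digital biomarkers), and then: "These profiles will subsequently be integrated to create digital phenotypes for individuals with SUD". The comparisons that are described concern algorithms. The neural network is the base, other learners are added, and "This multialgorithm approach will facilitate a comprehensive comparison of predictive accuracy across various models". Validation and Verification likewise compares models within each algorithm and across algorithms. Data Preprocessing adds a filter that selects features by their correlation with the target.

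**The concern.** The hypothesis lists sources of two kinds. The psychological tests already belong to the centre's routine. The band and the FER-based craving assessment are what the study brings in. One number, the performance of everything combined, is to speak for all of them.

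That number does not depend on whether the new sources contribute. The filter could drop every band and FER feature, the remaining questionnaire model could reach 0.80, and the Discussion's sentence would still read the result as a demonstration that includes band and FER data.

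At stake is what can be said about the wearable at the end. The study collects all the sources on the same participants, so their contribution can be examined. The stated criterion does not examine it.

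**Working it through.** **Is there a figure to reproduce?** No. The 0.80 cut-offs are chosen, not derived. The check is whether the rule can be met with no contribution from band or FER, and how readily.

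**Step 1: what the rule depends on.** Its inputs are the AUC and F2 of the integrated model. The article describes no model without a given source and no difference between source sets. The rule is therefore unaffected by the share of performance that comes from band or FER.

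**Step 2: where a pass without them is most plausible.** One task under the threshold is separating SUD patients from healthy individuals (Predictive Model). Controls must have no SUD history and no current substance use apart from caffeine (Control Participants). ASSIST is given at baseline to establish type, frequency and quantity of drug use, and Table 1 does not restrict it to the SUD group. If ASSIST enters the model, questionnaires could separate the groups almost by design. For therapy duration and relapse latency, nothing in the document indicates how well questionnaires would do.

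**Step 3: how often an uninformative band and FER would go unnoticed.** Assumptions:
- Band and FER carry no information.
- The other sources give a score with true AUC A. The document gives no value for A, so a range is shown.
- Scores are normal with unit variance in both groups, separated by d = √2 × Φ⁻¹(A). For A = 0.80, d = 1.414 × 0.842 = 1.19.
- Group sizes are 25 v 25 (the minimum per group under Sample Size) and 15 v 10. The latter applies the Introduction's 60% relapse rate to 25 patients: 0.60 × 25 = 15 relapsers, leaving 10.

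Simulated probability that the observed AUC is at least 0.80:

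| True AUC of the other sources | 15 v 10 | 25 v 25 |
|---|---|---|
| 0.60 | 4% | under 1% |
| 0.70 | 19% | 9% |
| 0.75 | 34% | 24% |
| 0.80 | 55% | 53% |
| 0.85 | 77% | 83% |
| 0.90 | 93% | 98% |

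Simulation error is about one percentage point. These figures use the AUC criterion alone, fit no model and score all participants. The article would test on one held-out fold, which is smaller.

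**Step 4: both criteria, with a fitted model.** A linear discriminant was trained on one questionnaire score plus two pure-noise sources standing for band and FER. Classes were balanced, the F2 cut-off was tuned on the training data, and testing used 2,000 new cases (300 runs per setting).

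| Questionnaire-only AUC | AUC and F2 both met, training n = 50 | AUC and F2 both met, training n = 400 |
|---|---|---|
| 0.80 | 16% | 40% |
| 0.85 | 86% | 100% |
| 0.90 | 93% | 100% |
| 0.95 | 99% | 100% |

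Across these settings, the mean AUC of the full model minus that of the questionnaire score ran from 0.782 − 0.801 = −0.019 to 0.950 − 0.950 = 0.000. A contrast between source sets would show that the added sources contribute nothing, while the absolute threshold is usually met once the questionnaires exceed 0.80 by a modest margin.

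**The case against.** The strongest reply is that the hypothesis is joint. It says that the listed sources together can support a model, and for that claim the performance of the integrated model is the matching criterion. This stands as a reading of the sentence. A reader might infer that the article claims the band or FER each add to the questionnaires. It does not say so, and no objective states an aim of added value. What remains is that the sentence names band and FER among what is demonstrated, and the next paragraph moves from a viable model to the device.

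That move is also hedged: a viable model could introduce the band as a complementary aid. The document does not tell centres to adopt it on the strength of the threshold, and it should not be read that way.

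A third reply is that assuming a questionnaire AUC at or above 0.80 and then finding the threshold often met is close to circular. That is fair if only high values are shown. A reader might infer that the criterion would pass in more than half of studies regardless. It would not: below a true AUC of 0.80 the chance falls quickly, as the first table shows.

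Finally, source-wise comparisons could sit in a fuller plan that is not shown, and nothing in the article bars them. Their absence is therefore not the point. The point is the inference that the article itself fixes, which an additional analysis elsewhere would not change.

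**Conclusion.** The point holds in a limited form. Meeting AUC and F2 of at least 0.80 would support a statement about the combined model. It would not support one about the smart band or FER, because the rule can be met when they add nothing.

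The size is conditional on the unknown questionnaire-only AUC. If band and FER are uninformative, the AUC criterion would be met in a small minority of studies at 0.60 to 0.70, in about half at 0.80, and in more than nine in ten at 0.90. With both criteria and model fitting, the figure at exactly 0.80 drops to 16% to 40%. The expectation that questionnaires do very well for SUD versus control rests on the control eligibility criteria and the content of ASSIST, not on a reported value.

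It would go too far to say that the study cannot answer whether the wearable helps. The data would allow the question to be examined, though imprecisely at this sample size.

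**What to change.** In Validation and Verification and in Principal Findings, state that the 0.80 thresholds describe the combined model only.

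For each prediction task, fit the base algorithm on the same participants and the same folds with four input sets:
- (a) demographic plus psychological data;
- (b) set (a) plus band data;
- (c) set (a) plus craving/FER data;
- (d) all four profiles.

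Base any statement about the band or FER on the paired difference in AUC between models with and without that source, with a bootstrap interval that resamples participants. Decide beforehand which set the Mannheimer Craving Scale belongs to: Table 1 places it with the craving assessment, while the text on the psychological battery lists it there.

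The cost is modest. Four input sets times three tasks (SUD versus control, therapy duration, relapse latency) make 12 base-algorithm analyses, of which the three with all profiles are already planned, so nine are added. No new data are needed. The Results section reports data still at labeling and preprocessing in June 2025, so there was room to specify this before modeling. The main downside is wide intervals at about 25 per group, so statements about individual sources may have to be labeled exploratory.

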### Limitations and Considerations

This study is subject to several limitations and potential risks of bias that must be acknowledged. Participants will be selected through convenience sampling of patients with SUD in a rehabilitation facility, limiting participation to cisgender male individuals between 18 and 59 years of age in both groups, therefore limiting the generalizability of results. The experimental status will be disclosed to them beforehand as well. This awareness could influence self-reporting in psychological tests and responses during exposure to visual stimuli related to substance use, potentially introducing bias.

While the Xiaomi Redmi Smart Band 8 has been selected for its cost efficiency and suitability for future clinical applications in rehabilitation centers, its sensors may have higher measurement errors compared to research-grade devices. Studies have indicated that similar consumer-grade devices generally exhibit lower precision. However, this trade-off is justified by the need to prioritize accessibility and scalability in clinical settings.

To identify events of physical activity, such as exercise, and atypical behavior, this study will rely in self-reporting through the app included in the Xiaomi Smart Band 8 device in the control group. Activity of participants with SUD will also be assessed by classifying their behavior according to the fixed schedule at the rehabilitation facility. Data will be clustered time-wise according to the time of the day and the reported activity accordingly, to reduce possible noise created by this variability. Since these events will rely on self-reported activities, a margin of error might be present in the observations in this time window.

Data clustering by groups before final testing introduces a potential risk that research staff may infer group assignments prematurely, which could influence the interpretation of results. The reliability of data used for training the models also depends on participants’ proper use of the device and the accuracy of self-reported information, both of which carry inherent risks of bias that may impact outcomes.

The characteristics of the data and the results of ML training, validation, and verification may affect the algorithm’s performance. There is a possibility that the baseline algorithm designed for this project might not achieve the desired accuracy or generalizability, based on the participants recruited by the cutoff time of recruitment. In addition, the possibility of an algorithm better suited for smaller sample sizes could be considered at a later stage of this study based on the available data.

To address these risks, the study will follow established guidelines for developing and reporting ML predictive models in biomedical research [103]. These guidelines provide a comprehensive framework for reporting in research articles and outline structured steps for model development, aiming to reduce bias and ensure robustness in predictive modeling [77].

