**Methods:**

The study will be conducted with adult male patients with SUD at a rehabilitation center and control volunteers. Participants will undergo a self-reported demographic and psychological assessment, a clinician-administered craving and emotional reaction test, and will also be monitored using a smartwatch. SUD participants will be monitored for a total of 18 months (6 months during rehabilitation, an additional 12 months post discharge), and control participants for a total of 6 months. All participants will be reassessed at the sixth month of monitoring. The collected data will then be used to train models with a neural network, which will then be validated against other models and compared with other algorithms. Demographic, psychological, digital biomarkers, and craving profiles will be created, correlations will be analyzed, and they will be compared with controls to generate a digital phenotype of SUD. When the model achieves adequate validity (area under the curve of ≥0.80), a graphic user interface will then be designed for clinical use.

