### Study Design

This study adopts a prospective cohort design, using data collected from nontraditional experimental groups to develop a MLM aimed at predicting clinical outcomes in the rehabilitation or relapse of patients with substance use disorders. The model will rely on comparative analyses between groups, identifying patterns in physiological, psychological, and emotional reactivity data to enhance predictive accuracy.

No interventions will be implemented in either group as part of this study, ensuring that all collected data reflect naturalistic conditions and minimizes external influence on the observed outcomes.

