### Timeline

This study will include 2 types of observations: continuous passive monitoring and active surveys conducted at specific time points. Passive monitoring will occur continuously for 6 months in both groups, followed by an additional year for participants with SUD after their discharge from the treatment facility. Active surveys will be conducted at three time points: (1) baseline session or baseline, (2) 3 months after baseline, and (3) 6 months after baseline.

For digital monitoring purposes, smart bands provided to participants will be synchronized with a smartphone at the baseline session. Psychological assessment will be conducted within the first 15 days after baseline. Retesting will take place during the 15 days prior to the 6 months after baseline. Emotional reactions to cravings will be assessed at two points: (1) 3 months after baseline and (2) at 6 months after baseline (Figures 1A-1F).

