#### Recruitment

Participants for the SUD group will be recruited from a male-only, age-restricted inpatient drug rehabilitation facility in Cajititlán, Mexico. Eligibility criteria include being male, aged 18-59 years, and actively participating in a therapeutic community treatment program for SUD, with a cognitive behavioral therapy approach. Furthermore, candidates must undergo their first rehabilitation attempt within this specific program and be under medication management for any possible mental health comorbidity diagnosed with the Mini International Neuropsychiatric Interview (MINI) or physical disease. Finally, participants are required to review the privacy and safety terms and provide informed consent before joining the study. Smartwatches will be synchronized with a community smartphone by the personnel of the rehabilitation center, in accordance with the restricted access to smartphones.

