#### Control Participants

Control group participants will be recruited through an open call for volunteers in the ZMG area, restricting the sampling to similar sex and age characteristics of the patients from the rehabilitation facility. To be eligible, individuals must be male, aged 18-59 years, have no history of SUD, either diagnosed or self-reported, with no current use of substances, excluding caffeine. They must review and agree to the privacy and safety terms, as well as the requirements for active participation. In addition, participants are required to commit to a six-month study period, synchronize and upload their data weekly, and attend scheduled meetings with the research team. In case an individual is interested in participating in the study, but does not have access to a personal smartphone, a device will be provided.

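### In the shared six months SUD status coincides with inpatient residence, so a SUD-versus-control AUC of 0.80 cannot be credited to SUD rather than to setting

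*Protocol article*

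**What the plan says.** **Where the groups live.** Under Recruitment: "Participants for the SUD group will be recruited from a male-only, age-restricted inpatient drug rehabilitation facility in Cajititlán, Mexico". Under Control Participants: "Control group participants will be recruited through an open call for volunteers in the ZMG area", restricted to similar sex and age.

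**When they are monitored.** The Abstract (Methods) says "SUD participants will be monitored for a total of 18 months (6 months during rehabilitation, an additional 12 months post discharge", and gives controls 6 months. Timeline confirms that passive band data are "followed by an additional year for participants with SUD after their discharge from the treatment facility".

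**How activity is identified.** Limitations and Considerations says that "this study will rely in self-reporting through the app included in the Xiaomi Smart Band 8 device in the control group". For the other group it says "Activity of participants with SUD will also be assessed by classifying their behavior according to the fixed schedule at the rehabilitation facility". Data are then grouped by time of day and reported activity, which the article describes as a way to reduce noise.

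**What the contrast is for.** Under Predictive Model: "A predictive model will be developed to distinguish between healthy individuals and patients with SUD", with AUC≥0.8 and F2≥0.8 as the threshold for a fully functional model. The Abstract says that comparison with controls yields the digital phenotype of SUD.

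**Which features enter.** Table 2 lists, among others, steps, sedentary time, activity intensity, time in bed, sleep midpoint and circadian rhythm measures.

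**What the limitations name.** They cover convenience sampling, awareness of status, device error, self-report error and staff inferring group. Confounding of diagnosis by setting is not among them.

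**The concern.** In the window that the two groups share, everyone with SUD is in a residential programme with a fixed timetable and every control lives in the community. A timetable plausibly shapes when people go to bed, when they get up, how much they walk and how long they sit. These are the quantities that the band measures.

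Age and sex restriction cannot separate diagnosis from residence, because the shared window contains no resident control and no free-living SUD group. Grouping by time of day does not help either. Within each time block the groups still differ by setting, and the activity label itself comes from a different source in each group.

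At stake is the meaning of two planned products: the phenotype and the healthy-versus-SUD classifier. Either could record residence rather than disorder, and could then fail to carry over once patients leave the centre.

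**Working it through.** **The plan's own figure.** The threshold of 0.80 is chosen, not derived, and no setting effect is given, so there is nothing to reproduce. The question is how large a setting effect would have to be to reach the threshold with no disease effect. The check covers the AUC part only, not F2.

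**Model (assumed).** Features are normal with equal variance in both groups. With D the standardised distance between groups, AUC = Φ(D/√2). For k features, each shifted by d SD in the same direction with common correlation ρ, D = d·√(k/(1+(k−1)ρ)).

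**Distance needed.** D = √2 × Φ⁻¹(0.80) = 1.190.

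**Shift per feature needed for AUC 0.80**, d = 1.190 × √((1+(k−1)ρ)/k):

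| Features k | Correlation ρ | Calculation | d (SD) |
|---|---|---|---|
| 1 | – | 1.190 | 1.19 |
| 4 | 0 | 1.190/√4 | 0.60 |
| 9 | 0 | 1.190/√9 | 0.40 |
| 5 | 0.3 | 1.190 × √(2.2/5) | 0.79 |
| 10 | 0.3 | 1.190 × √(3.7/10) | 0.72 |
| 5 | 0.5 | 1.190 × √(3.0/5) | 0.92 |
| 10 | 0.5 | 1.190 × √(5.5/10) | 0.88 |

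The correlated rows are the more realistic ones. Steps and sedentary time are linked, as are time in bed, sleep midpoint and circadian indices.

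**Sampling at the planned minimum of 25 per group** (simulation, one feature, setting shift only). The chance of an observed AUC of at least 0.80 is 12% at 0.8 SD, 29% at 1.0 SD, 53% at 1.19 SD and 85% at 1.5 SD.

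**Can existing data separate the two explanations?** Timeline and Table 1 provide band data for the SUD group after discharge, when participants no longer live at the facility. The article does not assign these data to the comparison with controls. Table 1 lists only the band and the PSQI after month 6; craving, picture-response and facial-emotion measures stop there.

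**The case against.** **The main models do not use this contrast.** This stands. The primary objective (Output) and all five output labels concern therapy duration and relapse latency within SUD, and so does the hypothesis in Principal Findings. A reader might infer that the whole predictive model is compromised; the document does not support that.

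**The article does not limit the contrast to inpatient months.** Partly stands. The restriction is inferred from the shared window. Figure 1 starts the SUD band after the first month of treatment, so six band months end near treatment month 7. A patient who completes within 7 months could be discharged before the window closes. Still, the Abstract describes these six months as spent in rehabilitation.

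**The naturalistic claim.** Study Design contains the words "ensuring that all collected data reflect naturalistic conditions". A reader might call this false for inpatients. The full sentence ties it to the absence of any study intervention, so it does not claim free living.

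**Schedule labels as model inputs.** A reader might infer that timetable-derived activity labels feed the classifier. Table 2 lists no such feature; the labels serve to identify and group activity.

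**The phenotype is more than the band.** It also integrates demographic, psychological and craving profiles. Childhood history and past substance use are not set by a timetable, and controls are selected for no SUD history and no current use. It is therefore too strong to say that the phenotype would largely describe institutional living.

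**First use is in the same centre.** The interface is meant for that facility, so inpatient data match its first setting. The Introduction also foresees monitoring patients in remission, where they would not.

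**Post-discharge data are selected.** This stands and limits the remedy. Relapse ends participation, so requiring six abstinent months would drop every early relapser. If the 60% relapse rate in the Introduction applied within six months (an assumption; no horizon is given), 25 × 0.40 = 10 participants would remain. This argues against moving the main contrast to that window.

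**Conclusion.** The point holds for the SUD-versus-control contrast only. In the shared window setting essentially coincides with group, so a healthy-versus-SUD AUC of 0.80 or more, or a band phenotype drawn from that comparison, cannot be attributed to SUD. Neither the time-of-day grouping nor the stated limitations address this.

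The required setting shift is 1.19 SD on one feature, about 0.4 to 0.6 SD on each of nine to four independent features, or about 0.7 to 0.9 SD on each of five to ten features correlated at 0.3 to 0.5. These figures rest on a normal, equal-variance model and on assumed shifts. They show that setting could reach the threshold, not that it will. The duration and relapse models are not undermined by this contrast.

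**What to change.** 1. Keep the inpatient contrast, but report it as *SUD in residence versus community controls*.
2. Name setting, and the different source of activity information in each group, as confounders in the limitations.
3. Prespecify a sensitivity analysis that repeats the contrast on band features alone, using the SUD participants' post-discharge abstinent days against the controls' data. Include the days before relapse from those who later relapse, where the timing is known.
4. State beforehand what counts as persisting discrimination. Describe the band component as a phenotype of SUD in general only if discrimination persists there.

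**Cost.** Analysis and reporting text plus one added analysis; the band data are already planned. Fewer SUD participants and days contribute, so the estimate is less precise. Those who contribute are selected by continued abstinence and are later in recovery, so lost discrimination would not prove a setting effect. The check cannot cover the craving or facial-emotion components, which have no data after month 6.
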